### ST Sessions

ST consists of seven 45-60-minute sessions. During the sessions, input and direction from the adolescents form the main lead regarding the exercises to offer adolescents a creative and alternative way to develop certain skills and to freely share their personal story. In this way, ST aims to add to more traditional modes that are not always tailored to the needs of adolescents [66]. This adheres to adolescents’ need for autonomy and control regarding their treatment [67]. Adolescents underscore their own voices and contributions as essential for successful therapy in order for therapists to really get to know their personal stories [68].

By incorporating mentalizing as the main therapeutic mechanism, ST aims to influence both treatment motivation and cognitive distortions. In order to develop the needed motivation to engage in treatment for behavioral change, it is in the first place necessary to acknowledge problematic behavior and to seek help for this behavior [69]. Additionally, someone must have the desire to behave more socially adequate and to formulate the kind of person someone would want to be in the future. Clustering these factors, te Velde et al [70] describe self-reflection as an important concept regarding treatment motivation. Since self-reflection is part of the definition of mentalizing, it is plausible that mentalizing can function as a therapeutic mechanism regarding treatment motivation. Besides, social perspective–taking is an important component of mentalizing [71]. By centering the exercises around that component, the incorrect or biased ways of attending or conferring meaning upon experiences (ie, the cognitive distortions) can be challenged [18]. Given its definition, the act of mentalization reflects the way in which an individual can give meaning to social experiences, namely, on the basis of inner mental experiences. By giving that way of meaning making a central role within the exercises and thereby helping adolescents improve the way they can make sense of their social world, mentalizing can function as a therapeutic mechanism regarding cognitive distortions as well.

The sessions are divided over 2 modules, A and B, which are executed in a fixed order. Before starting with the first module (ie, A), there is an intake session during which the adolescent chooses a personal learning goal. This goal focuses on mentalizing abilities, for example, “I want to learn that how I see a situation doesn’t have to be the same as how somebody else sees the same situation” or “I want to learn to listen to what somebody else thinks, feels, or would want to do in a situation so that I can better understand that person.” Each consecutive session ends with discussing the personal learning objective.

### Modules of the Sessions

#### Module A

Module A revolves around 3 main characters. Each session starts with watching a 360° VR video. This video (see Figure 3) is used to present the scenario and characters on which the exercises are based. The video shows a small group of guys in a park. Youngster 1 forces youngster 2 to beat up a passerby, youngster 3, and youngster 2 obeys. In between, there are fragments shown in which youngster 2 is interviewed about why he knocked down youngster 3. The video ends with a compilation of videos from the internet of real fights between adolescents. During watching, the video is streamed from the VR glasses to an extra screen, allowing the trainer to see what the adolescent is watching simultaneously. After watching the video, the adolescent chooses one of the 3 characters to focus on that session. Together with the trainer, the adolescent creates a backstory for the character based on various building block cards (see Figure 4), for example, for family, living situation, and sports. When the character has been given a personal story, the adolescent takes on the character’s perspective. Based on that perspective, linked to the created personal story, the trainer challenges the adolescent to reflect on the scenario from the video. After that, the adolescent switches back to their own perspective to discuss the differences and similarities between the 2 perspectives and why those might be present. Apart from watching the VR video, the exercises are performed outside of the VR environment. Figure 4 shows examples of the different cards that are used.

**Figure 3 figure3:**
[figure not shown]
Screen capture of the virtual reality video.

**Figure 4 figure4:**
[figure not shown]
Examples of the cards used in the sessions.

#### Module B

In module B, the exercises revolve mainly around a personal experience chosen by the adolescent. Adolescents visualize the scenario of this situation for the trainer by using Street View VR, which means that the adolescent will use the VR glasses to virtually go to the place of their personal experience. While virtually being present in that place, the trainer watches along with the stream of the VR glasses and the adolescent explains what exactly happened in that place. Thereafter, the same perspective-switching exercises as described above are executed but with different perspectives. One session is about the perspective from an unknown passerby, and the other session is about the perspective from someone in the social network of the adolescent. In an additional exercise, a fictional character is created. This character is put in different situations based on the situation cards, and the adolescent has to make and substantiate a choice in that situation based on the character. As in module A, in module B, all exercises take place outside of the VR environment as well. The use of VR serves to present a scenario on which the exercises will be based. During the last session, the trainer and adolescent reflect on the progress that has been made regarding the personal learning goal. They also evaluate the program all together and what the adolescent has learned in addition to the set learning objective. It is possible to involve, for example, the mentor in this final session and have the adolescent explain what has been done and learned.

### Training and Supervision

ST trainers receive a 2-day training course, provided by the first author and a highly experienced psychotherapist who is also a registered teacher and supervisor. The training focuses on the theoretical background of ST, working with VR, the ST protocol, and practicing the learned skills by participating in and reflecting on role plays with experience experts. In addition to the training, ST trainers are guided throughout the research period by participating in monthly supervision sessions. These sessions are also facilitated by the first author and the clinician from the ST training. Besides the supervision, trainers are encouraged to engage in peer consultation. Lastly, they are able to receive telephonic consultation by the first author or clinician on request. To gain insight into the extent to which trainers commit to the protocol, trainers are required to fill out session forms.

### Measures

#### Primary Outcome Measures

The main study parameters are assessed once a day in the format of an idiographic digital self-report questionnaire for the adolescents. The items are based on the questionnaires that are assessed at T0 and will be presented in a random order each day.

#### Treatment Motivation

Treatment motivation is measured using the Dutch Adolescent Treatment Motivation Questionnaire (ATMQ) [72]. The ATMQ consists of 11 self-report items with a 3-point Likert scale, ranging from “not true” to “true.” Reliability and validity proved to be good [72]. For the daily questionnaire, the ATMQ is included as a whole.

#### Cognitive Distortions

Cognitive distortions are assessed using the self-report How I Think questionnaire (HIT) [32]. The HIT contains 54 six-point Likert items that vary from “totally agree” to “totally disagree.” The Dutch version of the HIT showed acceptable reliability and validity [31,73]. To create the daily questionnaire, the subscale with the highest score will be selected.

#### Secondary Outcome Measures

The secondary study parameters include change in reflective functioning and social perspective–taking as well as a qualitative exploration of the overall experiences with regard to ST and VR.

#### Reflective Functioning

Reflective functioning is measured using the Reflective Functioning Questionnaire for Youths (RFQY) [74] and the Self-Reflection and Insight Scale for Youth (SRIS-Y) [75]. The RFQY is a 46-item self-report measure scored on a 6-point Likert scale ranging from “strongly disagree” to “strongly agree.” The questionnaire is adapted from the adult version, the Reflective Functioning Questionnaire [76], by rewording some items for a better developmental match. Both studies report preliminary support regarding reliability and validity. The RFQY consists of 2 scales, with a total RFQY score deriving from the sum of both scale scores. Higher scores indicate greater capacity for reflective function. The SRIS-Y is a 17-item, self-report questionnaire, answered on a 6-point Likert scale ranging from “disagree strongly” to “agree strongly.” The instrument consists of 2 subscales, Self-Reflection and Insight, resulting in 2 separate scores. The original adult version is reported as a reliable and valid measure of self-reflection and insight in adults [77]. Likewise, the SRIS-Y appears as a developmentally appropriate and psychometrically sound measure of self-reflection and insight in adolescents [75].

#### Social Perspective–Taking

Social perspective–taking is assessed using the Perspective Taking subscale of the Interpersonal Reactivity Index [78,79]. The Perspective Taking subscale consists of 7 items, answered on a 5-point Likert scale. The Dutch version of the Interpersonal Reactivity Index appears to be a psychometric adequate instrument [80].

#### ST Evaluation

The ST evaluation is done by conducting semistructured interviews with adolescents as well as trainers based on the Change Interview [81]. The purpose of the Change Interview is to obtain information about clients’ understanding about what has changed during therapy, why those changes have occurred, and what factors might have gotten in the way of change. By obtaining this information regarding ST, the interviews enable learning whether and, if so, what changes have occurred throughout ST from the adolescents’ and trainers’ perspectives. In addition, adolescents and trainers can clarify why they think those changes have occurred, referring to both therapy and extratherapy factors. Lastly, important information about hindering factors or possible negative changes regarding ST is gathered.

#### VR Evaluation

The VR evaluation is done by adding questions regarding this topic to the above-described interviews. All respondents are asked to reflect on their experience with VR in general and working with the VR material, what they believe VR did or did not add to ST, and what they think of the video used in ST. Additionally, they are asked how they think the VR component could be improved.

#### Sociodemographic Parameters

Sociodemographic information such as age, sex, education level, ethnicity, living situation, and possible experience with minor criminal activity is collected using a demographic questionnaire developed by the researchers. Information regarding diagnostic background and treatment history is collected using file information. When recent IQ data are missing, the Screener for Intelligence and Learning Disabilities [82] is administered.

An overview of all the measurement tools and data collection moments is given in Table 1 and Figure 5.

**Table 1 table1:** Overview of the measurement tools and informants.

Variable		Measure	Informant
**Primary outcomes**			
	Treatment motivation	ATMQ^a^: Daily questionnaire	Adolescent
	Cognitive distortions	HIT^b^: Daily questionnaire	Adolescent
**Secondary outcomes**			
	Reflective functioning	RFQY^c^, SRIS-Y^d^	Adolescent
	Social perspective-taking	PT^e^-subscale	Adolescent
	ST^f^ evaluation	Semistructured interview	Adolescent, trainer
	VR^g^ evaluation	Semistructured interview	Adolescent, trainer
**Other variables**			
	Demographics	Questions	Adolescent, clinician
	Diagnostic and treatment history	File information	Clinician
	Intelligence	File information, SCIL^h^	Clinician, adolescent

^a^ATMQ: Adolescent Treatment Motivation Questionnaire.

^b^HIT: How I Think questionnaire.

^c^RFQY: Reflective Functioning Questionnaire for Youths.

^d^SRIS-Y: Self-Reflection and Insight Scale for Youth.

^e^PT: Perspective Taking.

^f^ST: Street Temptations.

^g^VR: virtual reality.

^h^SCIL: Screener for Intelligence and Learning Disabilities.

**Figure 5 figure5:**
[figure not shown]
Overview of the data collection moments. ATMQ: Adolescent Treatment Motivation Questionnaire; HIT: How I Think questionnaire; IRI: Interpersonal Reactivity Index; PT: Perspective Taking; RFQY: Reflective Functioning Questionnaire for Youths; SRIS-Y: Self-Reflection and Insight Scale for Youth.

### Analysis

The primary outcome measures are the daily self-reported questions regarding cognitive distortions and treatment motivation. The resulting data will be presented as quantitative data. Within the context of SCED, including the multiple baseline design, the primary method for data evaluation regarding these repeated measurements is visual analyses [56,57]. This means that within-participants and between-participants data will be visualized graphically in order to explore the level and rate of change between the different phases. The slopes of the variables during the intervention phase will be compared to those of the baseline and follow-up data. The overall pattern in the data will be analyzed by examining whether scores overlap across phases. In order to evaluate the reliability of potential changes, 95% confidence intervals will be calculated for each participant by using standard errors of difference. Further, a standardized mean difference effect size will be calculated for each outcome variable, using “d-statistics” for SCEDs [83]. Additionally, repeated measures analyses will be conducted. Other procedures for SCEDs will be considered if necessary. The secondary outcome measures consist of the quantitative pre-, post-, and follow-up measurements as well as the semistructured interviews conducted during posttreatment assessment and long-term follow-up. The quantitative data will be analyzed by computing a Reliable Change Index for each measure [84]. Qualitative data will be analyzed using iterative thematic analysis [85]. The interviews will be recorded using professional recording equipment in order to transcribe and analyze the data. A statistics expert of the Clinical Monitoring Center of the Amsterdam University Medical Centers (Amsterdam UMC) will be consulted regarding data analysis.

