After the informed consent procedure, the researchers decide whether a participant is eligible to take part based on the inclusion and exclusion criteria. When necessary, a clinician will be consulted to make an informed decision. After official enrollment, premeasurements are conducted, and randomization takes place. Because trainers, clinicians, and adolescents will notice in which condition adolescents are participating, allocation is not blinded. Appointments for the ST-intake session and following sessions are made according to the randomization. Directly after the premeasurements have been conducted, the daily measurements are set up by installing the data collection app (m-Path). Everything about the app and data collection is explained as well as tested with the adolescent. From then on, the app automatically sends out notifications for the daily assessments within set time frames. This continues until the last day of the follow-up phase, according to the randomization. During the baseline and intervention phase, the researcher, ST trainers, and participants are in touch on a regular basis. Together, they check how things are going and whether there are any particularities regarding ST, the daily measurements, or in general. The intensity (eg, frequency, duration) of these contact moments will be kept the same across participants as much as possible. If necessary, for example, to encourage participants to fill in their daily measurements, the researcher will be in touch more often. Contact moments will be registered per participant in order to take possible variations regarding contact moments into account when analyzing treatment effects.

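### The primary outcomes are judged by eye with no stated decision rule and no masking of the graph reader described; a masked first reading would reduce reader bias at little cost

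*Protocol article*

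**What the plan says.** **Primary method.** The Analysis section of the protocol article states that "the primary method for data evaluation regarding these repeated measurements is visual analyses". Data within and between participants are to be "visualized graphically in order to explore the level and rate of change between the different phases", slopes are compared between phases, and "The overall pattern in the data will be analyzed by examining whether scores overlap across phases". No threshold or decision rule accompanies these judgements.

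**Other analyses.** The same section adds a 95% confidence interval per participant, a d-statistic for single-case designs per outcome, and repeated measures analyses. A statistics expert "will be consulted regarding data analysis".

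**Blinding.** The Procedures section says: "Because trainers, clinicians, and adolescents will notice in which condition adolescents are participating, allocation is not blinded".

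**Who is close to the intervention.** Under Training and Supervision, "ST trainers receive a 2-day training course, provided by the first author and a highly experienced psychotherapist". On the monthly supervision it says: "These sessions are also facilitated by the first author and the clinician from the ST training". The Procedures section adds: "During the baseline and intervention phase, the researcher, ST trainers, and participants are in touch on a regular basis".

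**Timing and structure.** The Results section places analysis after the end of data collection. The Design section randomises each participant to a 1-, 2- or 3-week baseline. The Sample Size section plans 18 participants in sets that each contain all three baseline conditions.

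**The concern.** The step that ranks first for both primary outcomes is a judgement by eye. A reader who knows where the phase change lies, and expects an effect there, can see level shifts, slope changes or non-overlap that a reader without that knowledge would not. With no decision rule, such a reading has no stated false-positive rate.

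The stated reason for not blinding concerns people who take part in or deliver the training. It gives no ground for leaving a later reader of graphs unmasked. The outcomes are self-reports by adolescents who know their phase, so expectation can already enter at the reporting stage. An unmasked reading could add a second source, and this one is avoidable. The involvement of the first author in training and supervision makes the question more than formal.

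**Working it through.** **1. The texts side by side.** The Procedures section gives one reason for not blinding and names three groups: trainers, clinicians and adolescents. The graph reader is not among them. The Results section puts analysis after data collection, when masking cannot interfere with scheduling or care. The reason given therefore does not extend to the reader, and a masked reading is feasible.

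**2. The plan's own figures.** Inputs from the Sample Size section: minimum 3 participants, 60% attrition, 2 settings, 3 baseline conditions. Taking the minimum of 3 as applying per setting (my reading): 3 / (1 − 0.60) = 7.5, rounded up to 8, then to 9 as a multiple of 3; 9 × 2 = 18. Then 18 / 3 = 6 sets, matching the six attempts stated. Masking changes none of this.

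**3. Chance level of a masked matching.** A set holds three series with baselines of 1, 2 and 3 weeks, so there are 3! = 6 possible assignments. If there is no effect and the display gives nothing away:
- one complete set fully matched: 1/6 = 0.167
- two complete sets both matched: (1/6)² = 1/36 = 0.028
- three complete sets all matched: (1/6)³ = 0.0046
- six complete sets, Binomial(6, 1/6): P(≥3) = 2906/46656 = 0.062; P(≥4) = 406/46656 = 0.009

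**4. How many sets may be complete.** The six-set figures hold only without attrition. Assume that losses are independent and that a lost participant's series is unusable.
- At 60% attrition, a set is complete with probability 0.4³ = 0.064. The expected number is 6 × 0.064 = 0.38. P(none) = 0.936⁶ = 0.67. P(at least two) = 1 − 0.672 − 6 × 0.064 × 0.936⁵ = 0.05.
- At 51%, the other rate cited in the article: 0.49³ = 0.118, and P(at least two) = 0.15.

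These are pessimistic. A participant who leaves during the intervention phase may still give a usable series. A set with two series left also carries information: if the reader is told which two baseline lengths are present, chance is 1/2! = 1/2. One complete set and two such pairs, all matched, have probability 1/6 × 1/2 × 1/2 = 1/24 = 0.042.

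**5. Does series length give the condition away?** Baseline and follow-up each last 1, 2 or 3 weeks around 4 intervention weeks. Paired inversely, the totals are 1+4+3 = 2+4+2 = 3+4+1 = 8 weeks, which fits the approximately 8 weeks in the Design section. Paired equally, they would be 6, 8 and 10 weeks and length alone would reveal the condition. The pairing is in Figure 1, which was not available in the text reviewed, so the display must be set to equal length for the 1/6 to hold.

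**6. What masking leaves untouched.** A simulation had a least-squares rule do the matching. Assumptions: 56 daily points, lag-1 autocorrelation 0.3, no true effect, and a pure shift in self-report at the phase change.

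| Reporting shift (SD) | Set correctly matched |
|---|---|
| 0 | 0.16 |
| 0.5 | 0.40 |
| 1.0 | 0.76 |
| 1.5 | 0.95 |

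A masked reader will thus detect a reporting shift as readily as a real change.

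**The case against.** The strongest reply is that the article names no graph reader and does not say whether that person sees phase labels. A reader might infer that the graphs will be read unmasked by the team that trains and supervises the trainers. The documents do not support that. Only the first author and one clinician are documented in those roles, a statistics expert is to be consulted, and a full protocol or analysis plan that is not shown may settle who reads what. This stands, and the point is confined to what the article fixes: a visual primary method, no stated rule, and a reason for not blinding that does not cover the reader.

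Second, the visual reading is not alone. The confidence intervals, d-statistic and repeated measures analyses need no graph reader and constrain the conclusion. That also stands, although the text presents them as additions to the primary method.

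Third, matching needs the phase lines removed, so it cannot replace the comparison of level, slope and overlap. This is correct, and is why the masked reading should come before that comparison and leave its status unchanged.

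Fourth, high attrition could leave too few complete sets to be informative. Step 4 bears this out in part: a single complete set cannot go below 0.167.

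**Conclusion.** The point holds as a recommended improvement. It is not an error or contradiction in the plan. The primary method leaves room for reader bias, the stated ground for not blinding does not cover the reader, and the randomised baselines offer a cheap check with a known chance level: 1/6 for one complete set and 1/36 for two. The figures 0.062 and 0.009 apply only if all six sets are complete, which the plan's own 60% allowance makes unlikely.

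A reader might also infer that masking would remove bias from the primary result. It would not. It reduces reader bias only; the self-report bias that the article itself concedes remains, as step 6 shows.

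The chance levels assume that the display reveals nothing about baseline length, that the reader does not recognise a series, and that loss of series does not depend on baseline length. The size of any reader bias cannot be estimated from the documents.

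**What to change.** Add a masked first reading to the Analysis section.

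- **Preparation.** The statistics expert already named there prepares each primary-outcome series without phase lines, labels or participant IDs and with equal displayed length, ordering the series at random and separately for each outcome. The expert does not do the reading.
- **Reading.** The analyst who would read the graphs anyway assigns the series of each set to the 1-, 2- and 3-week baselines and records this before labels are revealed.
- **Reporting.** Give the matching result for each of the two outcomes with its exact chance probability, computed from the series actually available. Both outcomes share one randomisation, so their probabilities should not be multiplied together.
- **Unchanged.** The labelled comparison of level, slope and overlap, the confidence intervals, the d-statistic and the repeated measures analyses stay as planned.

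**Cost.** A few hours of graph preparation; no extra reader, participants, visits or diary entries.

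**Downsides.** The matching tests only the timing of change and has little resolution if few sets are complete. A reader who has had contact with participants may recognise a series, so an analyst without such contact is preferable where the team has the choice.

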**Methods:**

The effects of ST are studied through a multiple baseline SCED, using both quantitative and qualitative data. In total, 18 adolescents from secure residential youth care facilities and secondary special education schools are randomly assigned to 1 of the 3 different baseline conditions. Throughout the baseline phase (1, 2, or 3 weeks), intervention phase (4 weeks), and follow-up phase (1, 2, or 3 weeks), daily measurements on treatment motivation and cognitive distortions are conducted. Secondary study parameters are assessed before baseline, after intervention, and after follow-up. Qualitative data are collected after intervention, as well as at 3 months and 6 months after the intervention.

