Participants are randomized to a 1-, 2-, or 3-week baseline phase. Randomization to varying baseline periods enables us to determine whether change in measurements is exclusively related to the application of the intervention. The random assignment is similar to the way in which a random assignment is used in between-participants designs [58]. The length of the phases has been chosen to keep them as short as possible in order to prevent dropout of the already difficult-to-reach target population. To assess primary outcomes, participants complete repeated measurements during a baseline phase (phase A), an intervention phase (phase B), and a short-term follow-up phase (phase C). These measurements are administered electronically once a day using a smartphone app. Phase A acts as a control and is therefore compared to phases B and C. To assess secondary outcomes, pre-(T0), post-(T1), and short-term follow-up measurements (T2), as well as qualitative data collection are used within the SCEDs. In total, the research period from the start of the baseline until the end of the short-term follow-up takes up approximately 8 weeks per participant. In addition to the short-term follow-up, qualitative data are also collected at 3 months and 6 months after T2. An overview of the study design is shown in Figure 1.

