### Sample Size

According to SCED research standards, SCEDs need at least 3 attempts to demonstrate an intervention effect. Each of these attempts needs to be at a different time point, requiring a multiple baseline SCED to have at least 3 baseline conditions. Additionally, each phase must include a minimum of 3, preferably 5, data points to qualify as an attempt to demonstrate an effect [59,63,64]. Regarding treatment attrition, a meta-analysis on inpatient juvenile offender treatment showed attrition rates of up to about 60% [17]. A study on residential treatment for adolescents with serious disruptive behavior problems reported that 51% had left the treatment center prematurely [65]. In order to adhere to the stated minimum of 3 participants by SCED research standards, while compensating for a potential 60% attrition rate, a total of 18 participants is strived to include in the study. The 18 participants are equally divided over the 2 research settings and the 3 baseline conditions. In combination with the daily repeated measurements, this sample results in 6 initial attempts to demonstrate an intervention effect of ST. An overview of the sample distribution is displayed in Figure 2. Each set consists of the 3 baseline conditions shown in Figure 1.

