ST trainers inform the researcher when the last ST session takes place. After the last session has taken place, 2 appointments are scheduled with the participating adolescent: 1 for the posttreatment assessment and 1 for the interview. This is done separately in order to reduce the burden on the adolescent. Additionally, 1 appointment is scheduled with the ST trainer for the interview with the trainer. After the last ST session, participants enter the follow-up phase. The researcher schedules the last appointment at the end of this phase to conduct the follow-up measurements and to close the study period together with the ST trainer and participant. At 3 months and 6 months after the end of the study period, the adolescents are approached again to participate in the 2 additional follow-up interviews. When a participant decides to leave the study prematurely, it is possible to finish the remaining ST sessions. The decision to do so or not will always be made in consultation with the trainer and clinician. Owing to the inevitable heterogeneity with regard to both the problems of the adolescents as well as the moment at which they participate in ST within their treatment process, no restrictions are imposed with regard to cointervention.

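### Causal attribution rests on the randomised baseline length, but no named quantitative analysis uses it, and the A-B intervals and effect size take in drift over study time

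*Protocol article*

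**What the plan says.** Protocol article, Design: "Participants are randomized to a 1-, 2-, or 3-week baseline phase". The reason given is causal: "Randomization to varying baseline periods enables us to determine whether change in measurements is exclusively related to the application of the intervention". The contrast follows: "Phase A acts as a control and is therefore compared to phases B and C".

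Protocol article, Analysis: visual analysis is the primary method for the daily measures, with graphs within and between participants. Intervention-phase slopes are compared with baseline and follow-up slopes, and overlap of scores across phases is examined. Each participant gets a 95% confidence interval from standard errors of difference, and "a standardized mean difference effect size will be calculated for each outcome variable". The list ends with "Additionally, repeated measures analyses will be conducted. Other procedures for SCEDs will be considered if necessary".

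Protocol article, Procedures: "no restrictions are imposed with regard to cointervention".

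**The concern.** Phase A always comes before phase B. Anything that moves scores over study time therefore enters the A-B difference alongside any effect of ST. The article itself points to several candidates:

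- Cointervention is unrestricted.
- School participants are screened in the first weeks of the academic year.
- The researcher makes extra contact where completion lags.
- Participants are selected for deficits in distortions or motivation, and the daily How I Think items come from the highest-scoring subscale. Both invite regression to the mean.
- The same items are answered every day.

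The staggered start is the design's protection: at the same study day, some participants have begun ST and others have not. The Design section relies on it, but none of the quantitative outputs named in the Analysis section makes that comparison. A steady drift towards improvement would appear in the mean differences of every participant and every baseline condition. It would look like a replicated effect, and the standardized mean difference would report it as benefit.

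**Working it through.** **Inputs from the article.** Phase lengths (Abstract, Methods): "Throughout the baseline phase (1, 2, or 3 weeks), intervention phase (4 weeks), and follow-up phase (1, 2, or 3 weeks". Sample size: "a total of 18 participants is strived to include in the study", divided equally over two settings and three baselines, which gives six sets of three. Attrition allowed for: 60%. The whole period is about 8 weeks, which fits 1+4+3, 2+4+2 and 3+4+1.

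**The plan's own figure.** 3/(1 − 0.6) = 7.5, so 8. Rounded up to whole sets this is 9 per setting, and 9 × 2 = 18. The article does not say that the minimum of 3 applies per setting, but this reading reproduces 18.

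**Assumptions.** The article gives no drift, SD or autocorrelation. I take a daily within-person SD of 1, a lag-1 autocorrelation of 0 or 0.3, and drift of 0 to 0.2 SD per week.

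**Bias of the A-B mean difference, no ST effect.** With a baseline of L weeks, phase A is centred at L/2 and phase B at L + 2. The bias under linear drift g is g(L + 2 − L/2) = g(L + 4)/2.

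| Baseline | Bias | g = 0.1 | g = 0.2 |
|---|---|---|---|
| 1 week | 2.5g | 0.25 SD | 0.50 SD |
| 2 weeks | 3.0g | 0.30 SD | 0.60 SD |
| 3 weeks | 3.5g | 0.35 SD | 0.70 SD |

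**Per-participant 95% intervals.** At g = 0.2 and no effect, the simulated interval excludes zero in about 26%, 44% and 65% of participants with independent days, and in 33%, 48% and 64% with autocorrelation 0.3. With no drift, autocorrelation of 0.3 alone gives about 15% to 18%.

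**Pooled illustration.** A t-test on the 18 A-B differences (autocorrelation 0.3, no effect) rejects in about 72% to 75% of simulated trials at g = 0.1 and in 100% at g = 0.2. The plan does not name this test; it shows only what pooling these differences would do.

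**Slope comparison.** Under constant linear drift the bias of the B-minus-A slope is about zero. If drift levels off as 0.6 × (1 − exp(−t)), t in weeks, it is about −0.37, −0.24 and −0.16 SD per week. The sign is opposite to the drift, so this bias need not favour ST, but it is still not an effect of ST.

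**Randomisation test.** Permuting baseline lengths within sets gives 6^6 = 46,656 assignments for 18 participants. With no effect it rejected in about 4% to 5% of runs at drifts of 0, 0.1 and 0.2. For an immediate shift, with all 18 retained, power was about 68% at 0.5 SD and 99% at 1 SD.

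**Limits of these additions.** At 60% attrition, 18 × 0.4 = 7.2 participants remain, and 6 × 0.4³ = 0.38 sets are expected to be intact. One intact set alone cannot give p below 1/6 = 0.167. Simulated power falls to about 6% for a 0.5 SD step and 12% to 13% for a 1 SD step. With all 18 retained but an effect that builds over the 4 intervention weeks, power is under 20%, and a model with study day and phase estimates the phase effect near or below zero.

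**The case against.** Three parts of the plan count against a broader charge.

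- A reader might infer that nothing planned uses the randomisation. The documents do not support that. Between-participants graphs are part of the primary visual analysis, and the Sample Size section requires attempts at different time points. Comparing staggered graphs is the informal way such a design uses its stagger. It remains a judgement: the article gives no criterion for it, and the design is nonconcurrent, so participants need not share calendar time.
- A reader might infer that every planned analysis absorbs any drift. The slope comparison does not: constant linear drift leaves the A and B slopes equal. The exposure concerns the mean-difference outputs for any drift, and the slopes only for non-linear drift.
- The repeated measures analyses are unspecified and could include time and phase. A condensed article may leave model terms to an analysis plan, and a statistics expert is to be consulted. This is fair, and missing terms alone would be no finding. What remains is a mismatch within the article: a strong causal claim in Design, and a list of quantitative methods of which none is stated to rest on the feature that carries the claim.

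It is also fair that a randomisation test is no cure. Its good power needs near-complete retention and an immediate effect. Neither can be counted on with attrition of up to 60% allowed for and a programme of seven sessions.

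**Conclusion.** The point holds in a limited form. The Design section credits the randomised baseline with more than the named quantitative analyses can deliver. The per-participant intervals and the standardized mean difference are open to drift of 2.5 to 3.5 times its weekly size. That multiplier follows from the stated phase lengths; the drift itself, the SD and the autocorrelation are assumptions, so 0.25 to 0.35 SD illustrates the exposure and is not a prediction. Slopes are protected against constant linear drift only, and use of the stagger rests on visual judgement. The documents do not show that the randomisation goes unused, nor that the eventual repeated measures model will omit time. Nor does the working support replacing visual analysis with a randomisation test or an adjusted model as the single main inference.

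**What to change.** - Keep visual analysis as the primary method.
- State that the repeated measures analysis includes participant, study day and phase, allows for autocorrelation, and treats study day flexibly enough to follow drift that levels off. Report its phase effect beside the unadjusted standardized mean difference and intervals.
- Add a supportive randomisation test for each primary outcome. It should permute baseline lengths as they were actually allocated, be evaluated over the common 8-week window, and have a rule for incomplete sets fixed in advance.
- Limit the claim of exclusive attribution in the Design section to what these analyses can support.

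The cost is wording and a short program; no further data or participants are needed, and the article places analysis after data collection. The adjusted estimate is less precise: in one simulation a participant-and-day estimate over study weeks 1 to 3 had a standard error of 0.24, against 0.11 for the unadjusted difference. Both additions are poor at detecting a gradual effect, and the randomisation test has little power at 60% attrition. The plan should therefore say beforehand that a non-significant result from either is not evidence of no effect.
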